### 2.2. Study Population and Participant Recruitment

The eligibility criteria for older adults in this study are as follows: (a) age 60 years or older; (b) residing in the community for at least six months with no plans to move out; (c) one participant in each household; and (d) voluntarily participating in the study and able to provide informed consent. Those who meet any of the following conditions are excluded: (a) having a physical health condition deemed unsuitable for influenza vaccination; (b) having a cognitive impairment or other severe illness that may affect the informed consent process.

In this study, we will collaborate with community health service centers to recruit study participants and carry out the project. Community collaborators will participate in the project training, assist with participant recruitment, support baseline and follow-up surveys, and assist in quality control.

### 2.3. Sample Size and Sampling

The primary outcome in this study is the influenza vaccination rate among older adults, assuming a two-sided test, a type I error rate (α) of 0.05, and a type II error rate (β) of 0.10. Based on a literature review, the current median influenza vaccination rate among older adults is 8% in China at national level [10], and the target vaccination rate after the IMB-based behavioral intervention is set at 16%. Accounting for the cluster sampling approach (with a design effect between 1.3 and 1.5), the required sample size per group is 72, for a total sample size of 576 participants. Assuming a 10% loss to follow-up in the final assessment, the total sample size is 640 participants, with 160 participants per arm, across two provinces and eight communities.

The client list of Essential Public Health Services in each community health service center will be used to facilitate participant randomization and recruitment. Within each participating community, a simple random sampling approach will be used to recruit 80 participants using computer-generated random numbers. All screening and recruitment will be carried out by the local staff working at the community health service center.

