## Abstract

**Background**: Influenza poses a substantial health burden, especially among older adults in China. While vaccination is one of the most effective preventions, influenza vaccine uptake rates among Chinese older adults remain low. This study examines the individual and combined effects of behavioral interventions based on the Information–Motivation–Behavioral Skills (IMB) model and economic incentives in promoting influenza vaccine uptake among older adults living in China. **Methods**: The study will recruit 640 older adults living in eight communities that have not been covered by the free influenza vaccination policy. These eight communities (as clusters), stratified by urban and rural, will be randomized to four parallel arms, including a usual care arm, an IMB-based behavioral intervention arm, a conditional economic incentive arm, and a combined behavioral-economic arm. The interventions will start from the beginning of the flu season and last for about one month. Specifically, the IMB-based behavioral intervention encompasses health education brochures, healthcare provider-led lectures, interactive quizzes, and personalized consultations. The exact number of economic incentives is conditional on the timing of vaccination (a higher amount for early immunization) and the number of people within a household to be vaccinated at the same appointment (a higher amount for more people). The primary outcome is the influenza vaccination rate. Data will be gathered through vaccination records and questionnaires covering IMB-based vaccination cognitions. Mixed-effects models will be used to analyze the outcome of vaccination rate, reporting difference-in-differences estimates with 95% confidence intervals. **Conclusions**: The results of this study have the potential to inform influenza vaccination program scaleup among older adults who are not yet covered by the free influenza vaccination policy. **Ethics and dissemination**: Ethics approval has been granted by the ethics commission of Peking University Health Science Centre (IRB00001052-24090). Participants will be required to sign a written consent form. Findings will be reported in conferences and peer-reviewed publications in accordance with the recommendations of the Consolidated Standards of Reporting Trials. **Registration number**: This study was registered at the Chinese Clinical Trial Registry (ChiCTR2400090229).

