## 1. Introduction

Influenza annually impacts a substantial fraction of the world’s population, causing significant health, social, and economic consequences. Globally, influenza causes an estimated 3 to 5 million cases of severe illness and 290,000 to 650,000 respiratory deaths annually [1]. Older people are generally more vulnerable to influenza. Research indicates that over 85% of influenza-related deaths occur among individuals aged 65 and above [2]. In mainland China, studies have estimated influenza-associated all-cause mortality rates of 14.33 per 100,000 persons for all ages and 122.79 per 100,000 persons for those aged ≥ 65 years [2]. This is accompanied by a significant economic burden among older people infected with influenza [3]. Research indicates that the average hospitalization cost for older adults due to influenza—around CNY 14,000–19,000 (approx. USD 1929–2618)—is double that of non-older adults, equating to roughly 60% of the average annual income of urban older adults and twice that of rural older adults [4].

Vaccination is the most cost-effective means of combating influenza [5]. Studies have shown that the influenza vaccine, aimed at protecting high-risk groups from severe influenza cases, effectively reduced hospitalizations for pneumonia or influenza by 27–60% and lowered the mortality rate by 48–80% in community-dwelling older adults [6,7,8]. The WHO recommendations underscore the necessity of annual vaccination for older adults aged 65 and above, urging/calling upon its Member States to achieve at least 75% vaccination coverage among older adults by 2010 [9]. In most regions of China, the influenza vaccine is not part of the national broad immunization program, and individuals must pay the market price (about USD 20) to get the vaccination. Despite the significant geographical variations, the overall rate of influenza vaccination of older adults remains low across the country, ranging from 33% to 46% in regions offering free vaccination and 0.5% to 5% in regions without free vaccination [10].

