## 2. Materials and Methods

### 2.1. Study Design

This study will use a cluster randomized controlled trial design, with the community as the unit of randomization and various interventions, to evaluate the effectiveness of IMB-based behavioral intervention and conditional economic incentives among the Chinese older adults. The primary outcome is influenza vaccination over the follow-up durations.

We will choose communities from different provinces where the influenza vaccine is not covered by the present health system and older adults needs to pay out of pocket. In the two targeted provinces (Jiangsu and Shandong), four communities will be selected from urban and rural areas within each province, resulting in eight communities in total. These eight communities will be stratified based on their urban or rural status and then randomly allocated to (1) the IMB-based behavioral intervention group, (2) the conditional economic incentives group, (3) the combined IMB-based behavioral intervention and conditional economic incentives group, and (4) the control group. We will assess influenza vaccine uptake before and after the intervention and between different study arms. Figure 1 illustrates the study design.

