### 2.6. Outcomes

The primary outcome is the influenza vaccination rate. The vaccination records will be collected from the collaborating health service center databases. This study does not provide free vaccination; participants need to pay for vaccination at the market price. The secondary outcome is the intention of influenza vaccination (under the free and paid scenarios), primarily from questions in the follow-up questionnaires.

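### The 8% planning control rate is a national median, while the trial recruits only self-pay communities, for which the Introduction gives 0.5%–5%; no reason is given for using it

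*Protocol article*

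**What the plan says.** Section 2.3 of the protocol article plans on the statement that "the current median influenza vaccination rate among older adults is 8% in China at national level", citing reference [10], and says that "the target vaccination rate after the IMB-based behavioral intervention is set at 16" per cent. The test is two-sided at 0.05 with a type II error of 0.10, and the design effect is 1.3 to 1.5. The section gives 72 per group and 576 in total, which becomes 640 (160 per arm) after 10% loss.

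The Introduction cites the same reference [10] for uptake by payment setting: "ranging from 33% to 46% in regions offering free vaccination and 0.5% to 5% in regions without free vaccination".

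Three places fix the setting as self-pay:
- The Abstract recruits from "eight communities that have not been covered by the free influenza vaccination policy".
- Section 2.1 chooses areas "where the influenza vaccine is not covered by the present health system and older adults needs to pay out of pocket".
- Section 2.6 adds: "This study does not provide free vaccination; participants need to pay for vaccination at the market price".

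**The concern.** A national figure spans regions where the vaccine is free and regions where it is not. The trial draws only on the second kind. Its planning control rate of 8% is above the top (5%) of the range that the article itself reports for that kind of region, and the article does not say why.

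This matters because the rate defines the effect the trial is planned to detect. From 8%, a doubling, a gain of 8 points and a target of 16% are all the same effect. From any rate between 0.5% and 5% they are three different effects with very different power. Section 2.3 states only the target rate and does not say whether it was chosen as a ratio, a difference or a fixed level. The power statement therefore does not describe the population being studied, and it cannot be carried over to that population without a further decision.

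**Working it through.** **Inputs.** Control rate 8%, target 16%, two-sided α = 0.05, power 90%, design effect (DE) 1.3–1.5 and 576 before loss, all from Section 2.3. Self-pay range 0.5%–5%, from the Introduction. The stated 72 per group must mean per community, since 8 × 72 = 576; that is 576/4 = 144 per arm. The loss step is consistent: 576/0.9 = 640.

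**Formulas** (pooled two-proportion test, p̄ the mean of p₁ and p₂):
- n per arm = [1.960 √(2p̄(1−p̄)) + 1.282 √(p₁(1−p₁) + p₂(1−p₂))]² / (p₂−p₁)²
- power = Φ{[(p₂−p₁)√m − 1.960 √(2p̄(1−p̄))] / √(p₁(1−p₁) + p₂(1−p₂))}, with m = 144/DE, that is 110.8 at DE 1.3 and 96 at DE 1.5.

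**Step 1: the plan's own figure.** For 8% versus 16%, p̄ = 0.12, √(2p̄(1−p̄)) = 0.4596 and √(0.0736 + 0.1344) = 0.4561. Then n = (0.9007 + 0.5845)²/0.08² = 345 per arm, or 449–518 with the design effect. The stated 144 per arm is not reproduced. One-sided tests, 80% power, a continuity correction, unpooled variance and the arcsine form do not give 72 or 144 per arm for a two-sample comparison either.

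Power at 144 per arm:
- DE 1.3: Φ[(0.8420 − 0.9007)/0.4561] = Φ(−0.129) = 45%
- DE 1.5: Φ[(0.7838 − 0.9007)/0.4561] = Φ(−0.256) = 40%

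This 40–45% is the comparator for everything below.

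**Step 2: position of 8% and 16%.** 8% exceeds 5%, the upper end of the self-pay range. 16/5 = 3.2, so the target is at least 3.2 times any rate in that range; from 0.5% it is 32 times.

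**Step 3: power at 144 per arm with self-pay control rates** (range over DE 1.5 to 1.3):

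| Control rate | Doubling kept | +8 points kept | 16% target kept |
|---|---|---|---|
| 5% | to 10%: 26–29% | to 13%: 49–55% | 70–77% |
| 2% | to 4%: 13–14% | to 10%: 65–71% | 93–96% |
| 0.5% | to 1%: about 6% | to 8.5%: 77–82% | 98–99% |
| *8% (protocol)* | *40–45%* | *40–45%* | *40–45%* |

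Only the doubling column falls below the comparator.

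**Step 4: rate detectable with 90% power at 144 per arm** (solving the power formula for p₂, DE 1.3 to 1.5):
- from 0.5%: about 10–12%
- from 2%: about 14–15%
- from 5%: about 19–20%
- from 8%: about 24–25%

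The detectable difference shrinks as the control rate falls.

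**Limits of the check.** The normal approximation is rough at the bottom of the range: 144 × 0.005 = 0.7 vaccinated controls are expected at 0.5%, against 7.2 at 5% and 11.5 at 8%. The protocol's design effect is taken as given, and the calculation compares follow-up proportions only.

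**The case against.** **The two figures do not conflict.** A national median of 8% and a self-pay range of 0.5%–5% can both be true, and Section 2.3 openly labels its figure as national. A reader might infer an internal contradiction or an arithmetic slip. The text does not support that: no sum is wrong on this point. What stands is that a national figure is applied, without a reason, to a population that excludes the free-vaccination regions.

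**A lower control rate need not cost power.** A reader might infer that the 8% rate is why the trial is underpowered. The figures do not support that either. Power is already 40–45% at 8% versus 16%, because 144 per arm falls well short of the roughly 345 needed before any design effect. Section 2.3 words its target as a rate, and if 16% is held, moving to a self-pay control rate raises power to 70–99%. Holding the 8-point gain also raises it. Only the doubling reading lowers it. This objection is correct, and it limits the point to the misapplied rate and the undefined effect.

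**The regional range may not fit these participants.** It describes regions. Nothing in the article ties it to the chosen communities in Jiangsu and Shandong, or to consenting residents aged 60 or over. Section 1 also cites a quasi-experimental trial in older Chinese adults with 20% uptake under usual care, so control uptake in a trial can exceed regional coverage. The payment setting of that trial is not stated, and Section 2.3 does not rely on it. This is a fair reason not to require the 0.5%–5% range. It does not justify 8%.

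**Conclusion.** The point holds as a misapplied planning assumption. The 8% rate lies above the whole 0.5%–5% range that the article gives, from the same reference, for the only kind of area it recruits from, and the 16% target is at least 3.2 times any rate in that range.

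The consequence is an undefined planning effect, with no fixed direction for power. With 144 per arm and the stated design effect, power over the self-pay range runs from about 6% to 99% depending on whether the ratio, the difference or the target is kept, against 40–45% at the protocol's own inputs. The shortfall at 8% versus 16% is a distinct and larger sample-size error, and correcting the control rate alone would not remove it. Equally, repairing that arithmetic with 8% left in place would still give a figure for a population that the trial does not recruit.

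The conclusion assumes 72 per community (144 evaluable per arm), a design effect of 1.3–1.5 and the pooled two-proportion approximation. It also assumes that the Introduction's range is a reasonable guide to the participating communities; a recorded local rate would override it.

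**What to change.** In Section 2.3:
1. Base the control rate on self-pay communities. The participating communities' recorded 2023–24 rate is preferable: Section 2.6 already draws outcome records from the centres' databases, and Section 2.5 asks about that season at baseline. Failing that, use the Introduction's 0.5%–5%. If 8% is kept, justify it for self-pay communities.
2. State the target effect as an absolute difference from that control rate.
3. Restate the power, or the detectable difference, for the fixed 144 evaluable per arm at the low and high ends of the range. At 90% power the detectable rates are about 10–12% from 0.5%, 14–15% from 2% and 19–20% from 5%.

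The cost is a short recalculation and revised wording, with no change to the design or conduct. The stated 90% power must be replaced by whatever the recalculation gives.

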### 2.4. Intervention

The intervention started before the influenza season, running from October this year to February next year. Before the start of the influenza season, the eight communities were randomly allocated into four study arms: (1) IMB-based behavioral intervention, (2) conditional economic incentives, (3) a combination of IMB-based behavioral intervention and conditional economic incentives, and (4) the control group with usual care, with stratification by urban and rural areas.

**IMB-based behavioral intervention.** The older adults will receive behavioral intervention based on the IMB model (Figure 2). The underlying idea of the intervention is that vaccination behavior is closely related to the older adults’ vaccine knowledge, their motivation to reduce the risk of influenza infection through vaccination, and vaccination-related behavioral skills. The IMB model includes the following components: (a) information, comprising objective and subjective vaccine information; (b) motivation, including perceived susceptibility, attitudes (towards vaccines), and complying with social norms (e.g., peer recognition of vaccine); and (c) behavioral skills, mainly encompassing vaccine-related self-efficacy (e.g., managing side effects), action planning (scheduling vaccinations), and coping planning (dealing with vaccination obstacles) [33]. The conditional economic incentives could lead to behavior change via potential pathways, involving modulating the price effect, enhancing the income effect, and mitigating high discounting or present bias [34].

The main components of the intervention, designed based on the IMB model, will be implemented offline and include the following:

(a) Distribution of health education brochures. The printed health education brochures summarizing official information on influenza vaccination from WHO and China’s National Health Commission will be distributed once after the baseline.

(b) Lectures on influenza vaccination. Influenza vaccination experts will lead the lectures. Topics will cover information about influenza vaccine, improving intentions for influenza vaccination uptake, social norms for vaccination, self-efficacy in vaccination and managing potential side effects, and creating effective action plans for vaccine appointments. The research team will provide lecture materials. This component will also take place once.

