(c) Interactive quizzes on influenza knowledge with prizes. Participants will engage in quizzes on influenza knowledge, using questions sourced from official core information. This activity will occur once.

(d) One-on-one consultations with doctors. Participants will have access to one-on-one consultations with doctors during the intervention period.

The intervention program will be implemented after the baseline assessment. The interventions will start at the beginning of the flu season and last for about one month. Supported by the research team, the community staff will be responsible for delivering the intervention and monitoring the process.

**Conditional economic incentives.** Two incentive conditions have been established: one is based on the timing of vaccination within the flu season, and the other is based on the number of people vaccinated together. First, each participant vaccinated within the first month of the flu season receives CNY 30 (or about USD 4.25 at current rates) as the early-bird incentive. The incentive is CNY 15 if the individual gets vaccinated within the second month and CNY 0 after the second month. Second, each participant receives CNY 30 if three or more people within the same household are vaccinated on the same day, while it is CNY 15 for two people and CNY 0 for one person vaccinated alone. The above two conditional incentives can be combined, offering a maximum total incentive of CNY 60 per person, which amounts to approximately 50% of the current market price for the influenza vaccination in 2024, set at CNY 114. Participants will be informed of the incentive system upon entering this study. The incentives will be delivered in cash after the verification of vaccination records.

**A combination of IMB-based behavioral intervention and conditional economic incentives.** Participants will receive both the IMB-based behavioral intervention and the conditional economic incentives during the intervention.

**Control arm: usual care.** Participants will receive usual care without additional interventions. This includes access to routine healthcare services, general health information available within the community, and informational posters in public spaces to promote influenza vaccination among all community members.

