### 2.5. Measurements

Participants will receive information about the study purpose, content, and procedures and sign a written informed consent form before the baseline assessment. Our research team independently developed the questionnaire regarding the scales used in the existing literature. The questionnaire includes the five main aspects: socio-demographic characteristics, vaccination intentions and status, vaccine literacy, and IMB-based vaccine cognization. A panel of specialists in epidemiology, psychology, and behavioral science will be invited to review and evaluate the face validity of the questionnaire and make the modification suggestions. The questionnaire will be tested on about 20 participants before formal use. Participants who complete the baseline and follow-up questionnaires will receive CNY 20 (≈USD 2.7) each time as compensation for their time.

**Sociodemographic characteristics:** Sociodemographic information will be collected, including gender, age, ethnicity, education level, occupation before retirement, place of residence, health status (including the presence of any chronic illnesses), personal monthly income, and insurance coverage status.

**Influenza vaccination intentions and status:** The vaccination intentions will be measured through questions assessing the participants’ willingness to receive the influenza vaccine in the current year. A five-point Likert scale ranging from “1 = strongly disagree” to “5 = strongly agree” will be used to capture their intention levels [35]. We will investigate the detailed information on the participants’ previous influenza vaccination experiences, encompassing their vaccination history in the last influenza season (from September 2023 to February 2024), the mode of payment for the vaccination, the accompanying individuals during the vaccination process, and any reasons cited for not being vaccinated. Information on pneumococcal vaccination status will also be collected.

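### Telling participants of the cash incentive on entry, with recruitment by staff of the body that delivers the intervention, leaves room for arm-dependent consent and for baseline intention answers that already reflect the offer

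*Protocol article*

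**What the plan says.** All references are to the protocol article.

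- **Who recruits (Section 2.3):** "All screening and recruitment will be carried out by the local staff working at the community health service center".
- **How people are chosen (Section 2.3):** "Within each participating community, a simple random sampling approach will be used to recruit 80 participants using computer-generated random numbers". The frame is the health centre's client list.
- **Who is eligible (Section 2.2):** one criterion is "voluntarily participating in the study and able to provide informed consent". One exclusion is "having a physical health condition deemed unsuitable for influenza vaccination".
- **When communities are allocated (Section 2.4):** "Before the start of the influenza season, the eight communities were randomly allocated into four study arms". Section 2.1 puts the allocation in the future tense. No recruitment date is given.
- **Who delivers (Section 2.4):** "the community staff will be responsible for delivering the intervention and monitoring the process", with support from the research team. The intervention follows the baseline assessment.
- **When the scheme is disclosed (Section 2.4):** "Participants will be informed of the incentive system upon entering this study".
- **When consent is taken (Section 2.5):** "Participants will receive information about the study purpose, content, and procedures and sign a written informed consent form before the baseline assessment".
- **Payments:** every participant receives CNY 20 for each completed questionnaire (Section 2.5). The incentive arms add CNY 0, 15 or 30 for timing and CNY 0, 15 or 30 for household members vaccinated together, at most CNY 60 (Section 2.4).
- **Analysis (Section 2.7):** difference-in-differences in uptake between each intervention arm and control, allowing for clustering.

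**The concern.** Randomising communities balances communities. It does not balance who agrees to take part within them if that decision is made when the arm is known. Here the arm-specific feature is a payment that depends on the primary outcome itself. A person who already plans to be vaccinated gains by joining an incentive community and has no matching extra gain in control. If such people join more readily in the incentive arms, recorded uptake rises there with no change in anyone's behaviour, and the result reads as an incentive effect.

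A second route runs through the baseline questionnaire. If the offer is known when the intention items are answered, baseline intention in the incentive arms is no longer a pre-exposure measure. That weakens it both as the baseline for the secondary outcome and as an adjustment variable.

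A third, smaller route is the exclusion for unsuitability for vaccination. It calls for judgement, bears on the outcome, and is applied by staff who may know the arm.

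**Working it through.** **1. The sequence, from the stated steps**

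- *Allocation.* Section 2.4 reports it as done before the season, while Section 2.3 puts recruitment in the future. Section 2.1 also has allocation in the future. The most that can be said is that allocation falls before or around recruitment.
- *Disclosure.* An arm-specific scheme can be explained on entry only if the arm is known by then. Section 2.5 has study content and procedures explained before consent, and consent signed before baseline. Read together, disclosure is apparently at or before consent and baseline.
- *Staff.* Sections 2.3 and 2.4 name the same body of local staff for recruitment and for delivery. The argument needs only that recruiters know the arm, not that one person does both.

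**2. What the random sample protects**

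The sample fixes who is approached. Enrolment still depends on consent and on the exclusion for unsuitability. The target is 80 × 8 = 640 enrolled, which is the whole planned sample. So the analysed set consists of people who agreed, whatever the rule for those who decline.

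**3. The difference in inducement**

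| | Control | Incentive arms |
|---|---|---|
| Two questionnaires | 2 × 20 = CNY 40 | CNY 40 |
| Conditional on vaccination, alone, first month | 0 | CNY 30 |
| Conditional on vaccination, maximum | 0 | CNY 60 |

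The difference between arms is CNY 0 to 60, paid only to those vaccinated. The maximum is 60/114 = 53% of the stated vaccine price.

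**4. What selection could do before any baseline correction (illustration)**

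Assume no true effect. Take the 8% planning rate (Section 2.3) as the share who would be vaccinated anyway. Suppose that in an incentive arm these people enrol *r* times as readily as others. The document gives no value for *r*. Then

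apparent uptake = 0.08*r* / (0.08*r* + 0.92), and spurious difference Δ = apparent uptake − 0.08.

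Since no one can consent with probability above 1, a given *r* is possible only if the others consent at a rate of at most 1/*r*.

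| *r* | Apparent uptake | Δ (points) | Others' consent at most |
|---|---|---|---|
| 1.25 | 0.100/1.020 = 9.8% | 1.8 | 80% |
| 1.5 | 0.120/1.040 = 11.5% | 3.5 | 67% |
| 2 | 0.160/1.080 = 14.8% | 6.8 | 50% |
| 2.5 | 0.200/1.120 = 17.9% | 9.9 | 40% |

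The planning difference is 16% − 8% = 8 points.

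**5. What difference-in-differences removes**

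Let *h* be last season's uptake among this season's would-be vaccinators and *l* that among the others. Selection raises the arm's baseline rate by Δ(*h* − *l*) and its final rate by Δ. On the risk-difference scale,

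residual bias = Δ − Δ(*h* − *l*) = Δ[1 − (*h* − *l*)].

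If the same people are vaccinated every year (*h* = 1, *l* = 0), the bias is zero. If past uptake says nothing about this season (*h* = *l*), all of Δ remains. The document gives neither *h* nor *l*, so for *h* at least as large as *l* the residual lies anywhere from 0 to Δ.

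**The case against.** The other side has several fair points.

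- **The order is not stated.** No recruitment date is given, Section 2.1 has allocation in the future, and Section 2.4 even writes the start of the intervention in the past tense, so tense is a weak guide. A reader might infer that recruitment definitely follows allocation. The document does not support that. What stands is that disclosure on entry presupposes a known arm.
- **Entry could mean just after consent.** If so, self-selection by participants closes. The baseline questionnaire could still follow the disclosure, and Section 2.5 points towards earlier disclosure.
- **The staff may be different people.** A reader might infer that the same individuals recruit and deliver. The document names only the same body. Experts lead the lectures, doctors give the consultations, and Section 2.2 describes collaborators as assisting with recruitment.
- **Control participants are paid too.** A reader might infer that control offers no cash reason to enrol. That is wrong: CNY 20 per questionnaire is paid in every arm. Only the payment conditional on vaccination differs.
- **A condensed article omits detail.** Consent wording and the handling of refusals may sit in the manuals and consent forms that Section 2.9 mentions. The absence of a concealment step is therefore not the finding. The finding rests on the stated timing of disclosure and the stated recruiters.
- **The analysis has a safeguard.** Habitual vaccinators drawn in by cash would raise the baseline rate as well, and difference-in-differences would subtract that part. It does not subtract new willingness this season among people not vaccinated last season.

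**Conclusion.** The concern holds as a risk of bias created by stated rules, not as a demonstrated bias. Two consequences follow from the text: consent may depend on the arm, and baseline intention in the incentive arms may be measured after the offer is known. Random sampling and difference-in-differences each reduce the first, and neither removes it.

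The size cannot be estimated from the document. A reader might infer a definite figure. For example, if 10% of incentive-arm recruits came for the cash and had 30% to 50% uptake anyway, the arm would rise by 0.10 × (0.30 − 0.08) = 2.2 to 0.10 × (0.50 − 0.08) = 4.2 points. Those inputs have no source in the document, and the sum ignores the planned baseline correction. The enrolment-ratio table above has the same limits. It shows only that moderate differences in consent could matter against an 8-point target, and that high consent among the others would cap them.

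The conclusion assumes that the arm is known to recruiters or participants by the time of consent or baseline. If it is not, the article needs only to say so.

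**What to change.** In all eight communities, complete sampling, eligibility screening, consent with one arm-neutral wording and the baseline questionnaire before the community's allocation and the incentive scheme are disclosed to recruiting staff or participants. In Section 2.4, change the sentence "Participants will be informed of the incentive system upon entering this study" so that the scheme is explained after the baseline assessment. Align the tenses in Sections 2.1 and 2.4 with that order. The intervention already follows baseline, so only the disclosure moves.

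If allocation is already known locally, the full remedy is no longer available. In that case:

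- use one arm-neutral recruitment script in every community;
- disclose the scheme only after baseline;
- adjust the primary model for last-season uptake;
- adjust also for baseline intention, but only if it was measured before disclosure.

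The cost is a second contact to explain the incentive in the two incentive arms and a minor change to the consent wording, which needs ethics approval and must fit the information promised before consent in Section 2.5.
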